### Study Design

The study design is a randomized controlled trial in which school groups (classrooms) will be randomized either to the intervention or control arm. Baseline measurements will be completed before group assignment, reducing the potential for selection bias. The randomization sequence will be generated using a computerized random number generator (IBM SPSS Statistics version 21.0) by a researcher not involved in the study. Classroom groups will be paired within each school and randomly assigned (1:1) to the intervention or control arm. Allocation will be revealed by the independent researcher only after baseline measurements are completed and the intervention curriculum has been designed. The study will be conducted over 1 year in 4 phases. In the initial diagnostic phase (phase 1), baseline obesity risk factors will be measured in both control and intervention arms, assessing family and sociodemographic variables (family interaction, diet quality at home, body image perception [BIP], and psychosocial well-being) and schoolchildren’s health variables (anthropometry, diet, and blood pressure). Parents in both arms will receive a report on their child’s diagnosis, and in the control group, some recommendations will be added to improve their health and eating habits. Phase 2 consists of implementing the curriculum during 4 months in the intervention arm. Phase 3, at the end of the intervention, consists of the evaluation of results from the intervention arm in terms of knowledge acquisition, effectiveness, retention, motivation to change, fidelity, and acceptability by schoolchildren; in both arms, changes in knowledge, anthropometrics, blood pressure, and behavior of schoolchildren in terms of diet quality, exercise practice, and sleep quality will be measured. Finally, in phase 4, after 6 months of the intervention, sustained changes in anthropometrics and behavior (same measurements as phase 1) will be measured. The study design is shown in Figure 1. The program will allow for ongoing contact with participants, thereby promoting their retention and measuring immediate and medium-term outcomes. Participants in the control group will receive a summary version of the intervention in the next school year.

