The present intervention protocol addresses childhood obesity in an integrative and unconventional manner, generating multifactorial knowledge about family behavior, individual factors, and the school environment. The aim of this protocol is to measure the effect of an intervention designed for low-income Mexican schoolchildren, focused on promoting healthy lifestyles for the prevention of obesity and cardiometabolic diseases. Specific aim 1 is to analyze whether baseline anthropometric and behavioral variables are associated with psychosocial well-being, family interaction or functionality, and perceptions of childhood obesity in the home environment. Specific aim 2 is to evaluate the effectiveness of the intervention in terms of retention, motivation to change, fidelity, and acceptability of the program by schoolchildren. Specific aim 3 focuses on evaluating changes in health behaviors at the end of the intervention and after 6 months in knowledge, diet quality, exercise time, and sleep time and quality.

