#### Assessment of Knowledge and Motivation for Change

Acquired knowledge, motivation for change, and satisfaction will be evaluated through a pretest and posttest. For motivation and willingness to change behavior [67], confidence and the importance attributed to the change are analyzed through 2 questions: “What level of confidence do you feel in being able to make this change?” on a scale of 1 (zero confidence) to 10 (extreme confidence); and “How important is it for you to make this change?” where 1 indicates little importance and 10 indicates the utmost importance [68].

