#### Effectiveness

Results obtained in the experimental arm will be compared with those of the control arm to analyze the significant differences in behavioral and health outcomes between them. This comparison will provide a more robust perspective on the real impact of the intervention on the habits and health of the participants [69].

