### Statistical Analysis

The normal distribution of the data will be verified using skewness, kurtosis, and Kolmogorov-Smirnov tests. Quantitative data with nonnormal distribution will be mathematically transformed for parametric analysis, or alternatively, nonparametric analysis will be used. Means and SDs will be calculated for continuous variables and percentages for categorical variables. To test age, sex, socioeconomic status, and location baseline differences, we will use chi-square tests for qualitative demographic variables (eg, socioeconomic level, family medical history, sport practice, etc) and analysis of covariance for quantitative variables (eg, anthropometrics, dietary intakes, HEI, TMexD, sleep time, BIP, family interaction, and psychosocial well-being). To evaluate specific aim 1, potential baseline associations of dependent variables (eg, anthropometrics and blood pressure) with independent behavioral variables (eg, dietary intakes, exercise and sleep time, family interaction, psychosocial well-being, and perception of childhood obesity) will be tested using multiple linear regression, starting with univariate regression (*P*<.2 and biological plausibility). Models will be built by a combination of univariate analysis and forward stepwise model selection using *P*≤.05 and biological plausibility. Preliminary models will be assessed for possible interactions (*P*≤.1) between sex and other variables included in the model, for collinearity (variance inflation factor<10), and for linear regression assumptions (linearity, normality, and homoscedasticity) using residual plots. Specific aim 2 will use mixed methods (qualitative and quantitative) to analyze results in terms of retention, fidelity, and acceptability of the intervention by children and school administrators. Specific aim 3 will compare the changes between the experimental arms (intervention vs control) from baseline to postintervention and to the 6-month follow-up in anthropometrics, blood pressure, HEI, dietary intakes, PA, sleep time, and knowledge. Primary analyses will follow the intention-to-treat principle. Given the hierarchical structure of the data (students nested within classrooms and classrooms within schools) and the repeated measurements over time (baseline, postintervention, and 6-month follow-up), intervention effects will be evaluated using multilevel mixed-effects regression models. Due to the cluster-based allocation, the intraclass correlation will be considered, potential attrition will be monitored, and all analyses will account for clustering to provide valid inferences. Models will include fixed effects for study arm, time, and the arm×time interaction, and random effects for classroom and school to account for intracluster correlation. Baseline values of the outcomes and covariates will be included as appropriate. Effect estimates with 95% CIs will be reported. We will examine model assumptions and fit indices. SPSS (IBM SPSS Statistics version 21.0) and STATA (StataCorp version 14.0) software will be used, with a *P* value <.05 for all statistical analyses.

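### Aim 2 counts motivation to change as effectiveness, but the plan evaluates it in the intervention arm and gives it no comparison with control

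*Protocol article*

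**What the plan says.** - **Introduction, specific aim 2.** The aim is to "evaluate the effectiveness of the intervention in terms of retention, motivation to change, fidelity, and acceptability of the program by schoolchildren".
- **Study Design, phase 3.** Two lists stand in one sentence. The first is "the evaluation of results from the intervention arm in terms of knowledge acquisition, effectiveness, retention, motivation to change, fidelity, and acceptability by schoolchildren". The second, which sets out what is measured, begins "in both arms, changes in knowledge, anthropometrics, blood pressure, and behavior of schoolchildren in terms of diet quality, exercise practice, and sleep quality will be". Knowledge is in both lists; motivation is only in the first.
- **Assessment of Knowledge and Motivation for Change.** "Acquired knowledge, motivation for change, and satisfaction will be evaluated through a pretest and posttest". Motivation is two items, confidence and importance, each scored 1 to 10. No arm is named.
- **Effectiveness (under Intervention Indicators).** "Results obtained in the experimental arm will be compared with those of the control arm to analyze the significant differences in behavioral and health outcomes". Whether motivation belongs to these outcomes is not said.
- **Statistical Analysis.** "Specific aim 2 will use mixed methods (qualitative and quantitative) to analyze results in terms of retention, fidelity, and acceptability of the intervention". Motivation is not named there. The aim 3 between-arm list covers anthropometrics, blood pressure, HEI, dietary intakes, physical activity, sleep time and knowledge, again without motivation.
- **Table 2.** The baseline row names knowledge but not motivation. Motivation appears at phase 3, among the intervention indicators.

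**The concern.** Retention, fidelity and acceptability describe how the program was delivered and received, and reporting them for the intervention arm is ordinary practice. Motivation is different. Table 1 lists reflective and automatic motivation among the components the program is built to change, and the two items can be answered by a child who attended no session. It is therefore an outcome for which a control value is meaningful.

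A change from pretest to posttest in one arm combines any program effect with whatever else moves the scores over a 4-month intervention: answering the same items a second time, growing older, and regression to the mean. A control arm randomized by classroom is visited at the same phase and could remove the part common to both arms. The plan as written does not use it for motivation, yet aim 2 would call the result effectiveness.

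**Working it through.** **1. Which comparison each place assigns to motivation**

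| Place | Role of motivation | Arm or comparison |
|---|---|---|
| Introduction, aim 2 | a term of effectiveness | not stated |
| Study Design, phase 3 | evaluated | intervention-arm list; absent from both-arms list |
| Assessment of Knowledge and Motivation | pretest and posttest | no arm named |
| Effectiveness | not mentioned | intervention vs control, behavioral and health outcomes |
| Statistical Analysis, aim 2 | not named | none |
| Statistical Analysis, aim 3 | not named | arm×time model for the listed outcomes |
| Table 2 | phase 3 indicator | not stated |

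No row gives motivation a comparison with control. If motivation falls outside the outcomes meant in the Effectiveness subsection, aim 2's use of the word has no comparison behind it. If it falls inside, the Study Design lists and the aim 3 list do not agree with that subsection.

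**2. Is there a stated figure to reproduce?** No. The document gives no effect size, SD, power or test for motivation. What follows is an illustration on assumed inputs and does not check a planned calculation.

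**3. Illustration: how often a one-arm pre-post test is significant with no program effect**

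From the document: 451 children (173 + 117 + 86 + 75 = 451), 24 classrooms, 12 per arm, 1:1 allocation of classrooms, significance at P<.05.

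Assumed: 225 children in the intervention arm (451/2 = 225.5; arm sizes are not given), two-sided testing, drift *d* in SDs of the change score, and ICC of the change score from 0.01 to 0.20.

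- Children per classroom: m = 225/12 = 18.75.
- Design effect: 1 + (m − 1) × ICC = 1 + 17.75 × ICC, which is 1.18, 1.89 and 4.55 for ICC 0.01, 0.05 and 0.20.
- SE of mean change, in SDs of change: √(design effect/225) = 0.072, 0.092 and 0.142.
- Probability of significance: noncentral t with 12 − 1 = 11 df, noncentrality d/SE, critical value 2.201.

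| Drift d | ICC 0.01 | ICC 0.05 | ICC 0.20 |
|---|---|---|---|
| 0 | 0.05 | 0.05 | 0.05 |
| 0.1 | 0.24 | 0.17 | 0.10 |
| 0.2 | 0.71 | 0.51 | 0.25 |
| 0.3 | 0.96 | 0.85 | 0.49 |

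Ignoring clustering (SE = 1/√225 = 0.067, normal critical value 1.96), the probabilities for 0.1, 0.2 and 0.3 are 0.32, 0.85 and 0.99.

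**4. What a between-arm contrast changes.** Drift common to both arms cancels, so it no longer raises the false-positive rate above about 0.05. With equal arms the SE grows by √2: from 0.067 to 0.094 without clustering, and from 0.092 to 0.130 at ICC 0.05.

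**The case against.** Several points on the other side stand, and they limit the claim.

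- **The intervention-arm list does not prove one-arm measurement.** It also holds knowledge acquisition, which the next clause measures in both arms, and effectiveness, which has its own between-arm definition. The subsection on the pretest and posttest names no arm. Control classrooms may have answered the motivation items; the document does not settle it.
- **No within-arm test of motivation is specified.** A reader might infer that ordinary drift will be declared a program effect. The document does not support that: it gives no pre-post contrast, no P value and no decision rule for motivation. The change can be misread; nothing says that it will be.
- **A reader might also infer that the trial's effectiveness as a whole is judged on one arm.** It is not. The Effectiveness subsection and aim 3 compare arms for health and behavior, so the problem is confined to motivation.
- **Table 2 is a summary.** Its baseline row also omits physical activity, which the Abstract lists among the initial measurements. It cannot be read as proof that no motivation pretest was taken, and the text states a pretest expressly.
- **Not every influence is shared by the arms.** Reports to control parents carry added recommendations. Intervention children also have three weekly sessions with staff, so any wish to please staff could differ by arm. A between-arm contrast removes only common drift.
- **The analysis of a process indicator may be left to a document not shown.** That could supply a missing model. It would not resolve the disagreement between the aim, the design lists and the definition, and it could not recover control scores that were never collected.

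**Conclusion.** The point holds in limited form. The aim counts motivation as effectiveness, the design sentence places it on the intervention-arm side, the analysis section gives it no between-arm comparison, and effectiveness is elsewhere defined as a comparison with control. A one-arm change in these two items would not support an effectiveness statement.

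The size of the possible error cannot be derived from the documents. The probabilities above rest wholly on assumed drift, ICC and arm size, and describe a test the protocol does not specify. They show only that modest drift could often reach significance in one arm. What aim 2 can conclude about motivation is affected; the health and behavior comparisons of aim 3 are not.

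**What to change.** The status table in Results marks the initial, final and 6-month measurements as complete in all four schools, so collecting new baseline or phase 3 answers is no longer an option. Data analysis is not yet marked complete in two of the four schools and interpretation in none, so the reporting rule can still be set.

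1. State whether the two motivation items were asked in control classrooms, and at which phases.
2. If they were, add motivation to the aim 3 outcome list and analyse it with the arm×time multilevel model already described, with random effects for classroom and school.
3. If they were not, report motivation as an uncontrolled descriptive process indicator and remove it from the effectiveness wording of aim 2.
4. In either case, bring into agreement specific aim 2, the two phase 3 lists in Study Design, Table 2, the subsections on motivation and on effectiveness, and the aim 2 and aim 3 sentences in Statistical Analysis.

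The cost is a few sentences, plus either a wider standard error (by √2 with equal arms) or a narrower claim.

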**Figure 1. F1:**
[figure not shown]
Study design for the ESCOLARISANO randomized controlled trial.

### Staff Training

Staff will be trained in data collection, intervention implementation, first aid, and childhood education techniques. Additional training is planned by community project experts to address different interventions.

### Selection of Schools

The districts and neighborhoods with the lowest economic resources in the region were identified using socioeconomic census data from the National Institute of Statistics and Geography (INEGI, for its acronym in Spanish), and 4 elementary schools were selected according to logistical feasibility and resources: 1 in Loma de Bácum (representing the rural area) and 3 in Ciudad Obregón, Sonora, México (representing the urban area). An interview will be held with the school principals to present the proposal, and those who agree will be asked for written authorization. Within each school, an equal number of groups (classrooms paired by grade) will be selected for the intervention and control arms, allowing for approximate matching of participants by sex and age in each arm. This approach allows us to offer the program to at least half of the students in each school and to implement the intervention in as many schools as possible according to available resources.

The number of classrooms per school is determined by the existing school structure and logistical feasibility. Across the 4 schools, a total of 24 classrooms will be included (12 in the intervention arm and 12 in the control arm), with varying numbers of students (participants) per classroom, since student grouping is pre-established by the Ministry of Education at the beginning of the school year.

### Participants

The inclusion criteria are being students aged 6 to 13 years enrolled in the selected schools, with availability to complete the intervention; residents of either Ciudad Obregón and/or Valle del Yaqui, Sonora; and having informed consent from a parent or guardian. The exclusion criteria are having any physical, metabolic, or mental illness that prevents them from carrying out the intervention or undergoing a health intervention program or diet, exercise, lifestyle, and/or therapeutic treatment in the 3 months prior to the study. Data collection instruments, questionnaires, and intervention activities were tailored for lower (children aged 6‐9 years, up to grade 3) and upper (children older than 9 years in grades 4 to 6) elementary school groups. For all school groups, a staff member acted as a support interviewer in the application of instruments and questionnaires.

### Program Promotion

A promotional campaign with flyers and posters will be conducted 1 month prior to the intervention both inside the schools and in nearby strategic locations. A face-to-face meeting will be held with parents where the program will be presented.

### Health Diagnosis

#### Family Medical History

The family medical history will be obtained before the intervention based on the Mexican Official Standard NOM-004-SSA3-2012 [35].

#### Anthropometric Measurements

Anthropometrics will be carried out in triplicate based on the methodology established by the World Health Organization [36] and Centers for Disease Control and Prevention [37].

##### Weight

A TANITA brand scale with integrated bioimpedance (model BC-533; Tanita Corporation of America, Inc) will be placed on a firm, flat surface. Participants must be barefoot, with their feet centrally positioned on the scale, arms at their sides, wearing as little clothing as possible, and avoiding carrying heavy objects (eg, belts, coins).

##### Height

A SECA 213 stadiometer (SECA Deutschland, Medical Scales and Measuring Systems) will be used. Participants must be barefoot and without any objects on their head (such as hairpins, buns, high hairstyles, and caps), standing with feet centered on the stadiometer and heels together at a 45° angle. The head, back, calves, heels, and buttocks must be in contact with the instrument, with arms falling naturally at their sides and the head in the Frankfurt plane [38]. The midsagittal line of the body must coincide with the midline of the instrument.

##### BMI and BMI Percentile

BMI will be calculated with the equation: BMI=(weight in kg)/(height in m^2^). BMI percentile will be calculated using the Centers for Disease Control and Prevention (2000) graphs, classifying participants as underweight, normal weight, overweight, or obese.

##### Waist Circumference Percentile and Waist-to-Height Ratio

Waist circumference (cm) will be measured with a Lufkin brand tape at the umbilicus level and classified as central obesity when it is above the 90th percentile [39], following the methodology proposed for Mexican schoolchildren and adolescents [40]. For the waist-to-height ratio, waist circumference will be divided by height (both in cm). Classification will be carried out according to the cutoff points proposed by Marrodan et al [41], with categories of overweight in boys with a waist-to-height ratio ≥0.48 and in girls ≥0.47; and obesity in boys ≥0.51 and in girls ≥0.50.

##### Body Fat (%) and Fat Mass Index

The measurement will be carried out using bioimpedance integrated into the TANITA scale (model BC-533; Tanita Corporation of America, Inc.), and participants will be asked to stand barefoot and in the Frankfurt plane, removing any metal and heavy objects that could interfere with the measurement. Body fat percentile will be calculated using the corresponding cutoff points [42]. Fat mass index, calculated by dividing kilograms of fat by height in m², will be classified into normal (≤) or overweight or obese categories (>) with limits of 7.76 in girls and 4.58 in boys from 8 years of age [43].

### Blood Pressure

The procedure will follow the NOM-030-SSA2-2009 [44] using a portable digital OMRON HEM-7120 blood pressure monitor. Measurements will be taken in triplicate on the left arm. Participants must be seated with back support, and measurements should be taken after 5 minutes of rest, leaving at least 2 minutes between repetitions.

### Family and Psychosocial Diagnosis

#### Family Interaction

Family interaction will be evaluated with the APGAR (Adaptability, Partnership, Growth, Affection, and Resolve) questionnaire, measuring family cohesion between parents and participants [45]. The response scale has the following measures: almost never, sometimes, and almost always. Scores (0 to 10) will be classified as follows: 0 to 2 indicates severe dysfunction; 3 to 6 indicates mild dysfunction; and greater than 6 indicates good functionality [46]. This questionnaire has been used in adolescents, schoolchildren, parents, and guardians and has been validated in its Spanish version [45].

#### Psychosocial Well-Being

We will have 2 versions of the Strengths and Difficulties Questionnaire adapted according to the age category: 4 to 9 years and 10 to 12 years [47]. It consists of 38 questions inquiring about emotional well-being, behavior, and social skills, including their relationships with themselves and others. This questionnaire has been used in school-aged children and adolescents in its validated Spanish version [48,49].

#### Body Image Perception

BIP will be assessed according to the methodology adapted by Collins et al [50] and validated for schoolchildren and adolescents. According to the authors, no cultural adaptation was required, as the instrument is based on visual figures and contains minimal textual content beyond instructions. It consists of 7 anatomical figures increasing in body volume, separately for male and female participants, representing different BMI percentiles. Participants will choose the figure that most closely matches their own silhouette, as well as the ideal silhouette they would like to resemble. Body image dissatisfaction will be assessed using a Likert scale questionnaire with response options of satisfactory, slightly satisfactory, and not at all satisfactory. Agreement of conformity will be assessed using the methodology adapted from Marrodán et al [51], comparing real BMI with perceived BMI, grouping participants into 3 categories: (1) values <−4 to −2, overestimate their BMI; (2) values between −2 and +2, perceive themselves as they are; (3) values between +2 and +4, underestimate their BMI. The feel-actual inconsistency index (feel-perceived weight status minus actual-real weight status) will be classified as follows: (1) score 0, consistency in the perception of weight status; (2) positive score, overvalued weight status; (3) negative score, undervalued weight status [52].

